### Sample size

Due to a shortage of similar studies, it is not currently possible to conduct a calculation of optimal sample size for this study. Based on existing knowledge about feasibility study methodology [6, 52, 54] and two feasibility studies of mHealth tool in public health settings [9, 26], we plan to recruit 70 patients. With 70 patients, the 95% confidence interval for a proportion estimate such as compliance would range between 0.38 and 0.62 (if the observed proportion is 0.50), which we consider acceptable for planning further studies.

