**Methods:**

The study is an investigator-initiated randomized controlled feasibility trial investigating the clinical mHealth tool *PTSD help* combined with care as usual (CAU) compared to CAU for adults with PTSD. Seventy patients will be recruited and receive either the mHealth intervention combined with CAU or CAU alone. The primary feasibility outcome is the proportion of eligible patients that participate in the study until the end assessment. Secondary outcome data consists of the fraction of compliant patients in the experimental group and exploratory data on *PTSD help* on PTSD symptom severity, level of psychological distress, sleep quality, dissociation symptoms, therapy readiness, quality of life, disability levels, and recovery.

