### Randomization

Randomization is conducted through the data management software REDCap, which allows a setup where no one from the research team has knowledge of or access to the underlying computer-generated allocation sequence. The randomization uses permuted blocks with varying block sizes based on a computer-generated allocation sequence created by a researcher with no affiliation to the project. The randomization allocation ratio is 1:1. This procedure ensures that researchers are blinded to the allocation process as the randomization allocation list, and block size is unknown to the researchers. The randomization procedure will be stratified by presence of Complex PTSD as measured with the International Trauma Questionnaire [18].

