### Procedure

Patients referred to CVD for diagnostic screening that are diagnosed with PTSD and accepted for PTSD outpatient treatment in MHS-CRD will be invited to participate in the study by the clinician conducting the screening. The invitation will include a leaflet with information about the study and contact information for the project. If the patient gives their consent for participation, he or she will be booked for an assessment interview. Patients who provide written consent and complete the assessment interview will be randomized if they fulfill the inclusion/exclusion criteria. After randomization, patients in the experimental group will be given immediate access to *PTSD help.* After 3 days, they will receive a phone call to ascertain whether they are experiencing any technical difficulties using the app. The second and third assessments will be administered electronically via a link to the questionnaires sent in an email through REDCap (see Fig. 1 for a consort diagram).

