### Feasibility outcome

The primary feasibility outcome is the proportion of eligible patients that agree to be randomized and participate in assessment 1 (T1, week 1) and 2 (T2, week 7). The secondary feasibility outcome is the fraction of compliant patients in the experimental group that is patients that actively use the system after. Compliance is defined as the use of *PTSD help* functions (excluding self-monitoring tools) corresponding to use twice a week (mean), assessed over 6 weeks pre-treatment, and during the psychotherapy treatment period. Compliance data is collected from the tracking log of the patient’s app activity through a secured webpage. In addition, compliance will be assessed through a *user behaviour questionnaire,* an 11-item questionnaire developed by the project group for the current study by selecting and modifying relevant items from questionnaires used in earlier studies evaluating the *PTSD Coach* app [34, 44] (see Additional file 1).

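### The precision quoted for compliance (0.38 to 0.62) is computed on all 70 patients, but compliance exists only in the roughly 35 app patients, where the interval is about 0.33 to 0.67

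*Protocol article*

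**What the plan says.** The Sample size section of the protocol article explains that an optimal sample size cannot be calculated. It points to feasibility methodology and two earlier mHealth feasibility studies, and then sets the target: "we plan to recruit 70 patients". One precision statement follows: "With 70 patients, the 95% confidence interval for a proportion estimate such as compliance would range between 0.38 and 0.62". The sentence closes with its condition and the sponsor's judgement: "if the observed proportion is 0.50), which we consider acceptable for planning further studies".

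Other sections fix who can contribute to compliance:

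- Feasibility outcome: "The secondary feasibility outcome is the fraction of compliant patients in the experimental group". Compliance itself is average use of the app's functions, other than self-monitoring, twice a week.
- Abstract, Methods: "Seventy patients will be recruited and receive either the mHealth intervention combined with CAU or CAU alone". The 70 are therefore the total over both arms.
- Randomization: "The randomization allocation ratio is 1:1".
- Procedure and the description of the app: access is given to the experimental group after randomisation, and the app is not generally available for download.

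The primary feasibility outcome, in the same Feasibility outcome section, has a different denominator again: eligible patients, counting those who accept randomisation and take part in the first and second assessments (T1 and T2).

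**The concern.** The precision statement names compliance as its example but uses the whole trial as the denominator. By the protocol's own definition, a control patient cannot be compliant or non-compliant, so about half of the 70 carry no information on this outcome.

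Two things make this more than a slip of wording. First, apart from the cited literature, this interval is the only number offered in support of 70 patients, and the sponsor's judgement of adequacy is attached to it. Secondly, the Background makes investigating compliance part of the aim before a larger trial, and the Statistical analysis section says that an efficacy trial will follow if the results indicate feasibility. A reader who relies on the printed interval will expect compliance to be known to within about 12 percentage points when the design delivers about 17.

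**Working it through.** **Inputs**

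- Total randomised: 70 (Abstract; Sample size).
- Allocation: 1:1 (Randomization). Hence 70 / 2 = 35 app patients. The article does not print 35; it is derived.
- Observed proportion: 0.50 (Sample size).
- Confidence level: 95%, two-sided (both limits are given).

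**Step 1: reproduce the plan's figure.** The Wald interval is p ± 1.96 × √(p(1 − p)/n). With p = 0.50 and n = 70:

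0.50 ± 1.96 × √(0.25/70) = 0.50 ± 0.117 = 0.383 to 0.617.

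This rounds to the printed 0.38 to 0.62. The exact (Clopper-Pearson) interval, 0.378 to 0.622, rounds to the same values. The printed figure therefore rests on all 70 patients.

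**Step 2: use the denominator that compliance has.** With p = 0.50 and n = 35:

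0.50 ± 1.96 × √(0.25/35) = 0.50 ± 0.166 = 0.334 to 0.666.

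The half-width grows by √(70/35) = √2 = 1.41, so the interval is about 41% wider.

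**Step 3: does the choice of method or the exact arm size matter?**

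| App patients | Method | 95% interval |
|---|---|---|
| 35 | Wald | 0.334 to 0.666 |
| 35 | Wilson | 0.343 to 0.657 |
| 35 | Wald, continuity-corrected | 0.320 to 0.680 |
| 35 (17 compliant) | Clopper-Pearson | 0.314 to 0.660 |
| 35 (18 compliant) | Clopper-Pearson | 0.340 to 0.686 |
| 34 | Wald | 0.332 to 0.668 |
| 36 | Wald | 0.337 to 0.663 |
| 30 (assumed, some app logs missing) | Wald | 0.321 to 0.679 |

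None of these comes near 0.38 to 0.62. To reach the printed precision for compliance, the app arm alone would need 70 patients, which means 140 randomised at 1:1.

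**Step 4: does the figure describe the primary outcome instead?** If 70 patients are randomised and a fraction u of eligible patients agrees, the denominator is 70/u. The protocol gives neither uptake nor T2 completion, so the following are assumptions, with 80% of randomised patients completing T2:

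- u = 0.50: N = 70/0.50 = 140, p = 0.50 × 0.80 = 0.40, half-width 1.96 × √(0.40 × 0.60/140) = 0.08.
- u = 0.70: N = 70/0.70 = 100, p = 0.70 × 0.80 = 0.56, half-width 1.96 × √(0.56 × 0.44/100) = 0.10.

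Both are narrower than 0.117. In general, if 70 are randomised the eligible denominator is at least 70, so 0.117 is an upper bound on the Wald half-width for this outcome.

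**The case against.** The strongest reply has four parts.

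1. **Compliance is only an example.** The sentence speaks of a proportion in general, and the Statistical analysis section also lists attendance at T2 and retention to the end of the study. For those, all 70 randomised patients are a natural denominator and 0.38 to 0.62 applies. This is true, but the Sample size section names none of them. The one outcome it does name is one for which the interval is wrong.

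2. **The primary outcome is not harmed.** This stands. Its precision is at least as good as the printed figure, and a separate precision line for it would be useful detail rather than the correction of an error. The shortfall concerns compliance alone.

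3. **The 70 was not derived from this interval.** This also stands. The section bases the number on methodology literature and earlier studies, and the interval illustrates what it delivers. But the sponsor's statement of adequacy is attached to that illustration, so the illustration has to be right.

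4. **Little depends on it.** Compliance is a secondary outcome, to be reported descriptively, and the article states no numerical compliance threshold, so no printed decision rule changes. In addition, 0.50 is the least favourable case: at an observed 0.80 with 35 patients the half-width is 1.96 × √(0.80 × 0.20/35) = 0.13. These points limit the consequence but leave the printed statement wrong.

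It might also be said that the Statistical analysis section names compliance as a binary outcome for logistic regression in its paragraph on between-group effects, as if both arms had compliance data. The definition cannot be applied to patients without the app, so this does not restore a denominator of 70.

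**Conclusion.** The concern holds. For compliance, the interval in the Sample size section is computed on twice the number of patients who can contribute. On the protocol's own definition and allocation, the interval at an observed 0.50 is about 0.33 to 0.67, not 0.38 to 0.62. The half-width is 0.166 against 0.117, and the conclusion is the same under the other interval methods and under small imbalances in arm size.

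The result assumes that 70 patients are randomised, that they split evenly, and that every app patient has usable log data; missing logs would widen the interval further. The printed figure is not the precision of the primary feasibility outcome either, but there it is conservative. It is correct for a proportion taken over all 70 randomised patients.

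**What to change.** In the Sample size section, replace the compliance statement with one on the right denominator, for example: with 35 patients in the experimental group, the 95% confidence interval for compliance would run from 0.33 to 0.67 if half of them comply. Then say explicitly whether about ±17 percentage points is enough for deciding on the larger trial.

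Keep 0.38 to 0.62, but attach it to an outcome measured in all randomised patients, such as T2 completion. Optionally, add a precision line for the primary outcome, with eligible patients as the denominator over a stated range of uptake.

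The cost is a corrected sentence or two and a less favourable precision for compliance. No patients need to be added, and no procedure or analysis changes.

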## Discussion

The aim of this trial is to investigate the feasibility of implementing a large scale RCT of the *PTSD help* app and to generate hypotheses about the effectiveness of *PTSD help* for psychiatric patients suffering from PTSD in a Danish psychiatric setting. The results of this trial will be used to inform a potential RCT by providing data for sample size estimation, optimizing the recruitment procedure with regards to the exclusion and inclusion criteria, identifying roadblocks for patients use of the app and supplying information about potential modification to the content of the app, both through analysis of the patients app use patterns, and responses on the user behavior questionnaires. In addition, as this is, to our knowledge, the first trial of a mHealth supplement for PTSD treatment is in a Danish population. This study may help increase our knowledge of possible benefits of, as well as potential barriers to, the implementation of mHealth tools. In the future, this may assist the development and implementation of mHealth tools for a range of psychiatric disorders. This may have the potential to increase therapy outcomes and decrease duration of suffering and the costs of treatment in the Danish psychiatric sector*.* In addition, this study can provide information on the effect of providing interventions in the pre-treatment period, as opposed to the waiting list condition. The measurements of clinical variables in this time period will also provide information on the effect of the pretreatment period.

As the study is a feasibility study, it has several limitations. First and foremost, due to the small sample size, it will be impossible to test the clinical effect on the various outcome measures. However, the relatively small sample size is deemed adequate to determine feasibility, which is the primary goal of the study. An additional limitation is that the study setting has made it impossible to create homogenous experimental and control therapy groups in the group setting, in that there will be a mix of patients from the two conditions in the therapy groups. Another limitation due to the study setting is that patient may receive a relatively wide variety of pharmacological treatments at different time points during the trial, information about which is not available to the research group due to GDPR rules limiting access to patient medical information. This lack of consistency in pharmacological treatment across patients limits the possibility to assess the direct impact of the app intervention, though this is partially mitigated by randomization. A general limitation in studies including mHealth tools in a psychiatric setting is that even though a large majority of adults have access to a smartphone, some do not, which will limit possible intake applicability of mHealth tools.

## Data Availability

The data of this study are available on request from the corresponding author [name].

## Abbreviations

C-PTSD: Complex PTSD
DSM-5: Diagnostic and Statistical Manual of Mental Disorders, Fifth Edition
DSS: *Dissociative Symptoms Scale*
ICD-11: International Classification of Diseases 11th Revision
IPT: International Trauma Questionnaire
MHS-CRD: Mental Health Services, Capital Region Denmark
MINI: *Mini International Neuropsychiatric Interview*
NEQ-rev: *Negative events and results of psychological treatment–revised*
PCL-5: *PTSD checklist for DSM-V*
PTSD: Post-traumatic stress disorder
RCT: Randomized controlled trial
SCI: *Sleep Condition Indicator*
SCL-10: *The Symptom Checklist-10*
*SCL-90*: The Symptom Checklist-90
SDS: Sheehan Disability Scale
SPIRIT: Standard Protocol Items: Recommendations for Interventional Trials
URICA-S: *The University of Rhode Island Change Assessment Short version*
WHO-5: The WHO-Five Well-being Index
